**9. Summary of the OSUCCC Data and Safety Monitoring Plan**

The Ohio State University Comprehensive Cancer Center [OSUCCC] places the highest priority on ensuring the safety of patients participating in clinical trials. Every therapeutic interventional trial conducted at the OSUCCC must include a plan for safety and data monitoring. Specific plans may vary based on the degree of risk involved in participation and the size and complexity of the clinical trial. The development of protocol monitoring plans and reporting requirements are dependent upon the study sponsor, nature of the investigational agent, and phase of trial. Trials include studies of cytotoxic and cytostatic agents in treating cancer in an active disease or adjuvant setting, agents targeting biologic endpoints, and interventional studies in cancer control and cancer prevention. Clinical trials sponsored by the NCI Cooperative Group Program [CALGB, GOG, NSABP, CCG, ACoS, RTOG, and SWOG] will be monitored by long-standing and established systems for cooperative group data submission, reporting, review, and monitoring.

All local, investigator-initiated therapeutic clinical trials, such as this proposal, are required to have specific data and safety monitoring plans based on the size and complexity of each trial and the potential risk to patients. Local, investigator-initiated Phase I trials are required to be continuously monitored by the principal investigator of the study with quarterly safety and monitoring reports submitted to the CCC Data and Safety Monitoring Committee [DSMC]. Local, investigator-initiated Phase II protocols will require monthly monitoring by the principal investigator of the study with biannual reports submitted to the DSMC.

Phase I/II studies sponsored by NCI/CTEP will be monitored by the principal investigator with required reporting to NCI/CTEP using the Clinical Trials Monitoring Service [CTMS], the Clinical Data Update

System [CDUS], and/or the Adverse Event Expedited Reporting System [AdEERS]. Due to the difficulty in accessing this data for data and safety monitoring locally, investigators of NCI-supported studies outside the cooperative group mechanism must report to the DSMC as required for local investigator-initiated phase I/II trials. Local, investigator-initiated randomized Phase III clinical trials will be monitored by protocol-specific data and safety monitoring boards [DSMB]. Formal DSMBs will consist of clinical investigators, biostatisticians, clinical trial experts, and lay patient advocates independent of investigators involved in the design and conduct of the trial. Following protocol review and monitoring, all DSMB recommendations and reports will be forwarded to the IRB, DSMB, the CCC Associate Director for Clinical Research, and the principal investigator.

All data and safety monitoring reports for local, investigator-initiated studies will include the number of patients entered, number of patients treated, dose level of agent[s] involved, summary of all adverse events reported to date using CTCAE 3.0 grading, a specific list of adverse events requiring expedited reporting to include ALL serious adverse events [SAEs], and, on an annual basis or as it arises, significant literature reporting developments that may affect the safety of participants or the ethics of the study.

Data safety and monitoring activities for each study will continue until all patients have completed their treatment and all patients are beyond the time point at which study-related adverse events would likely be encountered. Multi-center, limited-institution randomized phase III trials will be held to the same standards as local, investigator-initiated phase III trials and be required to submit formal data and safety monitoring plans including the establishment of an appropriate DSMB prior to activation.

All serious adverse events experienced by patients at the OSUCCC will be immediately reported to the

OSUCCC Clinical Trials Office, the DSMC, the Cancer IRB, and the study sponsor.

Protocol administration and individual patient clinical data will be subject to random audits by the OSUCCC

Office of Protocol Compliance to insure data accuracy and compliance with protocol-directed patient management. In the event that data and safety monitoring by the DSMC results the Associate Director for Clinical Research suspending or terminating a trial, the principal investigator, the OSUCCC Director, the Cancer IRB, the CSRC, and the study sponsor [to include NIH, Department of the Army, pharmaceutical industry sponsors, and other external sponsors] will be notified within 24 hours of such action.

The OSUCCC DSMC will additionally submit an annual report to the OSUCCC Director and OSUCCC

Associate Director for Clinical Research on activities of the past year and make recommendations to improve data and safety monitoring activities. All data and safety monitoring plans, institutional as well as individual protocol-specific, must be reviewed and approved by the OSU Cancer IRB prior to protocol initiation.

**10. Risks and Benefits**

**Risks**: The risks associated with this protocol are expected to be modest. Participants will complete functional and strength testing that has been shown to be of minimal risk of injury or physical discomfort. Men with any medical conditions that would increase the risk of completing these tests or participating in regular, personalized moderate intensity exercise will be excluded from participation. Any physical injury or discomfort will be infrequent, mild, and should not have any long-term effects. To ensure participant safety, all testing and exercise sessions will be conducted under the supervision of an experienced exercise and fitness professionals who is CPR-certified.

As for risk associated with the iDXA scan, additional ionizing radiation has the potential to damage proteins in the body, including DNA, as well as contribute to the subject’s accumulated radiation over time. There are no common adverse effects from bone densitometers and concern is limited to the overall accumulated radiation of each subject.

**Confidentiality:** Patient confidentiality of records will be maintained. Individuals will not be identified by name or by any other personal identifying information in laboratory records, reports, or publications resulting from this study. Thus, risk of disclosure of confidential medical information will be essentially nonexistent. Additionally, all data will be number coded and stored in a locked research office that can only be accessed by the research staff. These procedures have been successfully used to protect confidentiality in both [name] and [name] prior completed research.

**Benefits**: The benefits to the participant are significant. Men enrolled in the diet and exercise arm may improve their fitness over the course of the three month study. Men may feel more energetic, confident and activities of daily living may be easier. Additionally, the combination of diet and exercise counseling may facilitate weight loss in men who are overweight which can result in improved health and self image. All men who participate in this clinical trial will potentially have feelings of self-satisfaction for having contributed toward scientific understanding of prostate cancer treatment. Additionally, we will provide a $25 cash incentive for the completion of each major assessment visit (baseline, month 2, month 3, and month 6-8) for a total of $100 for study completion.

**11. Project Timeline**

Database development and personnel training will occur in the first 2 months of Year 1. Participant recruitment, with a target accrual of 3-5 participants per month, will begin month 4 of Year 1 and continue through month 7 of year 2. The intervention data collection will begin in Month 6 of Year 1 and end in month 10 of Year 2. The remaining months of Year 2 will be used for data analyses, presentations, and manuscript preparation and provide flexibility in the event of unexpected barriers during data collection.

Table 1. Timeline for performance of major study activities.

|  | Year 1 | Year 2 |
| --- | --- | --- |
| Activity | 1 2 3 4 5 6 7 8 9 10 11 12 | 1 2 3 4 5 6 7 8 9 10 11 12 |
| Database Development & Training | X --------- |  |
| Recruitment | X -------------------------------- | ------------------------- |
| Intervention & Follow-Up Data Collection | X-------------------------- | ------------------------------------- |
| Analyses/Presentations |  | X------------- |

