This protocol addresses a single-blind, 2-arm randomized controlled pilot study of an intensive lifestyle exercise and dietary intervention in PC patients undergoing prolonged ADT. The primary objective of the Intensive Diet and Exercise Adherence-Pilot (IDEA-P) trial is to determine the feasibility and preliminary efficacy of delivering a combined exercise and dietary counseling intervention to prostate cancer patients undergoing ADT. Preliminary data and effect size estimates obtained from this pilot study will be used as the foundation for the design of larger clinical exercise intervention studies in this priority population of prostate cancer patients. A total of 40 to 50 men undergoing ADT who plan to continue ADT for the next 3 months, will be randomly assigned to receive either the lifestyle exercise and dietary intervention (n=20-25) or standard of care disease management education (n=20-25). Assessment of all functional, anthropometric, and QOL outcomes will be obtained at baseline, after completion of the intervention at 2 months, at a follow-up visit 3 months following the baseline assessment, and at a final follow up visit scheduled between 6 and 8 months following baseline (see Figure 2: Study Design).

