**6.5 Methods for Both Arms (n = 40-50).** Men expressing an interest in the study will complete a brief screening interview to verify eligibility for inclusion in the trial. Men who meet the inclusion criteria can then sign the consent form during the clinic visit. Participants will complete the Dual-energy X-ray Absorptiometry (iDXA) scan anytime within one month of signing consent. The iDXA will be completed using the high definition GE Lunar iDXA. The iDXA machine is located in the gymnasium of Martha Morehouse, the same building at the Oncology Clinic. All other study visits will be conducted at the Recreation and Physical Activity Center on The Ohio State University main campus. **Please see the appendix for a detailed table of study visits**. At the baseline visit, the study will be explained in greater detail to the participant and all questions will be answered. The baseline visit will be comprised of anthropometric assessments, followed by the functional battery, and exercise and nutrition questionnaire assessments (the questionnaires can be completed at home if preferred by the participant) and finally randomization to either the Exercise and Diet Intervention arm or the Standard of Care arm. Participants will be given the option of completing the questionnaire assessments using the online RedCap data acquisition system. The OSU CCTS Research Informatics Services Core will be used as a central location for data processing and management. Vanderbilt University, with collaboration from a consortium of institutional partners (including OSU) and the NIH National Center for Research Resources, has developed a software toolset and workflow methodology for electronic collection and management of research and clinical trial data. REDCap (Research Electronic Data Capture) data collection projects rely on a thorough study-specific data dictionary defined in an iterative self-documenting process by all members of the research team with planning assistance from the CCTS Research Informatics Services Core. As part of the data dictionary development process, individual fields can be denoted as “identifiers”. When exporting a de-identified dataset, these variables are omitted. Additionally, the data export tool also allows for the shifted of dates for a limited data set export. REDCap provides a secure, web-based application that is flexible enough to be used for a variety of types of research, provides an intuitive interface for users to enter data and has real time validation rules (with automated data type and range checks) at the time of entry. It offers easy data manipulation with audit trails and ad hoc reporting functionality for reporting, monitoring and querying patient records, and an automated export mechanism to common statistical packages (SPSS, SAS, Stata, R/S-Plus). REDCap is 21 CRF Part 11 capable. Currently, REDCap installations support electronic signatures by positively identifying the user through a unique username and password combination. The provisioning of accounts and user access to specific database(s) is integrated with the OSU Medical Center LDAP authentication service, and the provisioning of access and specific user rights are managed by CCTS staff. The use of this technology will streamline subject visits and provide the capacity for precoding research data for export and analysis. Participants will be provided verbal and written instructions on how to wear the objective physical activity monitor (LIFECORDER Plus accelerometer) and will wear it for the next 7-days. Monitors will be returned to trial staff via U.S. postal service. Participants will return for three additional assessment visits: two months after baseline, three months after baseline, and between six and eight months after their baseline visits, and assessments identical to that at baseline will be obtained. Assessment of all functional, anthropometric, and QOL outcomes will be obtained at baseline by project staff who are blinded to participants’ treatment arm assignment.

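### The project timeline closes follow-up three months after recruitment ends, so men enrolled in the last three recruitment months cannot have the 6–8 month visit

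*Protocol*

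**What the plan says.** Section 11 (Project Timeline) states that recruitment "will begin month 4 of Year 1 and continue through month 7 of year 2", at a "target accrual of 3-5 participants per month". On data collection it says: "The intervention data collection will begin in Month 6 of Year 1 and end in month 10 of Year 2". The matching row of Table 1 is labelled "Intervention & Follow-Up Data Collection", so the end date covers follow-up as well as intervention data. The remaining months of Year 2 are for analysis and writing, and are also meant to "provide flexibility in the event of unexpected barriers during data collection".

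The visit schedule runs longer. Section 1 ends the assessments "at a final follow up visit scheduled between 6 and 8 months following baseline". Section 6.5 (Methods for Both Arms) has participants return "two months after baseline, three months after baseline, and between six and eight months after their baseline visits". Section 10 pays an incentive for the month 6–8 visit and counts it towards study completion. Both appendix schedules, for the intervention and the standard-of-care groups, place this visit at weeks 24–32.

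Two places still describe a study whose last visit is at 3 months: the Approach paragraph that opens Section 6, and the standard-of-care paragraph in Section 6.5.

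**The concern.** The timeline allows three months between the last enrolment and the end of data collection, while the visit schedule needs at least six. If the calendar is followed as written, men who enrol late miss the final visit because the study has closed, not because they dropped out.

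This matters because the trial is a feasibility pilot. Objective 2 (Section 3) and the feasibility measures in Section 7 rest partly on retention. Section 6.5 also intends to evaluate uptake of independent exercise over months 2–8. Men cut off by the calendar would thin the only data collected after month 3. If they were counted in the retention denominator, retention would look worse than it was.

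**Working it through.** **Inputs**, with months counted from the start of Year 1:

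- Recruitment runs from Year 1 month 4 to Year 2 month 7, which is study months 4 to 12 + 7 = 19. That is 19 − 4 + 1 = 16 months (Section 11).
- Data collection ends in Year 2 month 10, which is study month 12 + 10 = 22 (Section 11).
- The final visit is 6–8 months after baseline (Sections 1, 6.5 and 10; appendix).
- Accrual is 3–5 men per month (Section 11), for 40–50 men in total (Sections 1 and 6).
- Assumption: each man's baseline falls in his month of recruitment.

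**Reproducing the stated end date.** End = last recruitment month + last visit. With a last visit at 3 months, 19 + 3 = 22, which is exactly the stated end. With a last visit at 6–8 months, 19 + 6 = 25 to 19 + 8 = 27, which is Year 3 months 1–3. The stated end date follows only from a 3-month design.

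**Who is cut off.** The latest baseline that allows a 6-month visit is 22 − 6 = month 16. Months 17, 18 and 19 miss it, which is 3/16 = 19% of the recruitment window. The latest baseline that leaves the whole window open is 22 − 8 = month 14. A man enrolled in month 15 can be seen up to 22 − 15 = 7 months after baseline, and one enrolled in month 16 only at 22 − 16 = 6 months.

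**How many men.** Study months 4–16 are 13 months, so the number with a reachable final visit is 13 × rate, capped at the total enrolled.

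| Accrual | Enrolled | Baseline by month 16 | No 6-month visit |
|---|---|---|---|
| 5/month | 40–50 | 13 × 5 = 65, so all | 0 |
| 4/month | 40–50 | 13 × 4 = 52, so all | 0 |
| 3/month, stopping at 40 | 40 | 13 × 3 = 39 | 1 |
| 3/month to month 19 | 16 × 3 = 48 | 39 | 9 |
| Even, 40 over 16 months (2.5/month) | 40 | 32.5 | 7.5 |
| Even, 50 over 16 months (3.125/month) | 50 | 40.6 | 9.4 |

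**Effect on apparent retention in the slowest stated case.** Take the protocol's 20% attrition and assume that it applies at the final visit and is unrelated to enrolment date. Then 0.8 × 39 = 31 of 48 men (65%) have a final visit, against 0.8 × 48 = 38 (80%) with no cut-off.

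**Sensitivity.**

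- If data collection uses the slack to Year 2 month 12 (study month 24), the latest baseline for a 6-month visit is 24 − 6 = month 18. Month 19 still misses it.
- If the window opens at week 24 exactly (24 × 7 / 30.44 = 5.5 months), the cut-off covers 19 − (22 − 5.5) = 2.5 recruitment months instead of 3.

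**The case against.** The strongest reply is that this is a projected calendar and not a rule for ending follow-up. Nothing in the protocol says that late enrolees will be dropped. At 4 or 5 men per month enrolment would be complete by month 16 and nobody would be lost. Section 11 also keeps some slack at the end of Year 2. This stands in part: it limits the size of the problem and makes it a consistency error rather than a design flaw. It does not remove the conflict. The slack stops one month short, and the recruitment window itself matches slow accrual, since 40–50 men over 16 months is 2.5–3.1 per month, around the lower end of the stated range.

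A second reply is that the stated end date concerns intervention data only. The Table 1 label, which names follow-up explicitly, rules that out.

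Four stronger readings are tempting, and the documents do not support them:

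- **That five recruitment months (5/16 = 31%) are lost.** This treats an 8-month visit as required. A visit at 6 months satisfies the window, so men enrolled in months 15–16 can still be seen.
- **That month-3 values would be carried forward to stand for months 6–8.** Section 8 limits the efficacy tests to months 2 and 3 and applies last value carried forward to data missing through attrition. It states no efficacy analysis at 6–8 months, and calendar cut-off is not attrition.
- **That the efficacy tests are damaged.** The 3-month visit just fits, since 19 + 3 = 22.
- **That baseline may fall up to a month after consent, which would widen the gap.** The one-month allowance in Section 6.5 is for the iDXA scan. No interval is given for the baseline visit. Any lag would enlarge the shortfall, but the protocol gives no figure for it.

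**Conclusion.** The timeline is wrong as written, on a limited scale. It fits a last visit at 3 months and contradicts the 6–8 month visit required elsewhere in the same protocol. The likeliest explanation is that Section 11 was not updated when that visit was added. This is an inference from the exact fit of 19 + 3 = 22 and from the two paragraphs that still describe a 3-month study.

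Men enrolled in the last 3 of 16 recruitment months cannot reach the final visit. At the stated accrual rates that is between 0 and 9 men; even accrual of 40–50 men over the whole window gives about 8–9. These counts assume that baseline falls in the month of recruitment and that data collection stops at the end of study month 22. The consequence is confined to the final follow-up, retention and months 2–8 adherence data.

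**What to change.** Bring Section 11 and Table 1 into line with the visit schedule in one of two ways.

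1. Move the end of follow-up data collection to study months 25–27 (Year 3 months 1–3) and place the analysis after it. The cost is an extension of a few months beyond the two-year plan, which Section 8 ties to the time and resources of the funding mechanism.
2. Keep the end at study month 22 and set the last baseline at study month 16 (Year 2 month 4), with the latest enrolees seen at the start of the window. The cost is a tighter enrolment window: 13 months × 3–5 = 39–65 men, one short of 40 at the lowest rate.

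If neither is done, state that men enrolled after study month 16 will have no final visit. Report them as administratively missing at that visit, leave them out of its retention denominator, and do not carry earlier values forward for them.

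In the same amendment, reconcile the Approach paragraph of Section 6 and the standard-of-care paragraph of Section 6.5, which stop at 3 months, with the rest of the protocol.

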**12. References**

**APPENDIX**

**Study Schedule for Diet and Exercise Intervention Group**

|  |  | | **Month 1** | | | | **Month 2** | | | | **Month 3** | | | | **Months 6-8** |
| --- | --- | --- | --- | --- | --- | --- | --- | --- | --- | --- | --- | --- | --- | --- | --- |
|  | **Oncology**  **Clinic**  **Visit** | **Baseline**  **and Randomization** | **Week**  **1** | **Week**  **2** | **Week**  **3** | **Week**  **4** | **Week**  **5** | **Week**  **6** | **Week**  **7** | **Week**  **8** | **Week**  **9** | **Week**  **10** | **Week**  **11** | **Week**  **12** | **Weeks 24-32** |
| **Sign Consent** | **x** |  |  |  |  |  |  |  |  |  |  |  |  |  |  |
| **iDXA Scan** | **x** |  |  |  |  |  |  |  |  |  |  |  |  | **x** |  |
| **Physical Assessment**  **(*functional and strength battery, anthropometric measures)*** |  | **x** |  |  |  |  |  |  |  | **x** |  |  |  | **x** | **x** |
| **Supervised Exercise Sessions** |  |  | **2x** | **2x** | **2x** | **2x** | **2x** | **2x** | **x** | **x** | Frequency determined by participant | | | |  |
| **Behavioral Counseling** |  |  | **x** | **x** | **x** | **x** | **x** | **x** | **x** | **x** |  |  |  |  |  |
| **Behavioral Follow up by telephone** |  |  |  | **x** |  | **x** |  | **x** |  | **x** |  | **x** |  | **x** |  |
| **Nutrition Counseling** |  |  | **x** | **x** | **x** | **x** | **x** | **x** | **x** | **x** |  |  |  |  |  |
| **Nutrition follow up by telephone** |  |  |  |  |  |  |  |  |  |  | **x** |  | **x** |  |  |
| **Quality of Life Questionnaires** |  | **x** |  |  |  |  |  |  |  | **x** |  |  |  | **x** | **x** |
| **Behavioral & Feasibility Questionnaires** |  | **x** |  |  |  |  |  |  |  | **x** |  |  |  | **x** | **x** |
| **National Institutes of Health FFQ and Fruit & Vegetable Screener** |  | **x** |  |  |  |  |  |  |  |  |  |  |  | **x** | **x** |
| **Three Day Diet Records** |  | **x** |  |  |  |  |  |  |  |  |  |  |  | **x** | **x** |

